## Abstract

**Background:**

A major challenge for primary care is to set priorities and balance demands with available resources. The registered nurses in this study are practice nurses working in primary care offices, playing a large role in initial assessments. The overall objective of this research is to investigate practices of communication and decision-making during nurses’ initial assessment of patients’ health problems in primary care, examine working mechanisms in good practices and develop feasible solutions.

**Methods:**

Project PINPOINT aims for a prospective multicenter study using various methods for data collection and analysis. A purposive sample of 150 patient‒nurse consultations, including 30 nurses and 150 patients, will be recruited at primary care centers in three different geographic areas of southwest Sweden. The study will report on outcomes of communication practices in relation to patient-reported expectations and experiences, communication processes and patient involvement, assessment and decision-making, related priorities and value conflicts with data from patient questionnaires, audio-recorded real-time communication, and reflective interviews with nurses.

**Discussion:**

This research will contribute to the knowledge needed for the guidance of first-line decision-making processes to best meet patient and public health needs. This knowledge is necessary for the development of assessments and decisions to be better aligned to patients and to set priorities. Insights from this research can empower patients and service providers and help understand and enhance feasible person-centered communication strategies tailored to patients’ level of health literacy. More specifically, this research will contribute to knowledge that can strengthen nurses’ communication, assessments, and clinical decision-making in primary care. In the long term, this will contribute to how the competencies of practice nurses and other professionals are organized and carried out to make the best use of the resources within primary care.

**Trial registration:**

ClinicalTrials.gov Identifier: NCT06067672.

## Background

One of the core functions of primary care is first contact accessibility to healthcare. In Sweden, over 36 million health visits are made annually in primary care, and more than 10 million of these are visits to registered nurses (RNs), i.e., practice nurses working in primary care offices [1]. These nurses play a large role in initial assessments and are usually the first primary care contact for the patient. The initial assessment in patient-RN encounters is a prerequisite for subsequent actions that need to be taken so that the right patient ends up at the right time in the right place. Correctly performed, the assessment safeguards the quality of care and decreases preventable healthcare costs, hospitalization and visits to the emergency department [2, 3]. However, nursing practice on assessments and decision-making processes in primary care has received limited attention in research. As a consequence, there is a lack of knowledge of the working mechanisms and processes related to RNs’ communication with patients and assessments. Disseminating and implementing good RN practices will contribute to making primary care fit for the future.

Currently, healthcare is under increasing pressure as a result of shortages in financial and human resources, a rapidly aging population with more long-term conditions and multimorbidity needing primary care [4]. RNs have a prominent role and could contribute considerably to ensuring equal and person-centered primary care and the delivery of sustainable care [5, 6]. Nursing consultations have been shown to achieve similar or better health outcomes in primary care when compared to physicians [7] at lower costs. Optimizing RNs’ role and responsibility could therefore improve primary care services.

In this research, we focus on patients’ first point of contact, i.e., persons seeking primary care for a new health concern or a new episode of a problem [8], different from more continuous primary care over time. Given the variety of patients of all ages and their health complexities, assessments and priorities are demanding. A correct assessment is needed for RNs to make decisions and priorities meeting the urgency and severity of the patient’s health condition. Consequently, decision-making and priority setting can be complex and may have negative consequences for quality of care [9, 10]. This complexity results from conflicting goals, restricted access to services and waiting lists, profitability, and the need to safeguard high-quality care, patient safety and person-centredness. All these circumstances may jeopardize the healthcare system and healthcare professionals’ performance [11].

RN’s communication with the patient is the basis for the exploration and understanding of patient health concerns [12]. It also has therapeutic value, as it can lead to better health outcomes for patients, more effective processing of information, improved adherence to treatment and advice, and higher patient satisfaction [13–15]. Communication is fundamental for sharing expertise, building a trustful relationship and decision-making [16]. In contrast, instances of miscommunication can be linked to problems such as impaired patient safety and poor patient experiences [14, 17]. Moreover, communication with patients can improve the level of health literacy among the public, a rarely noticed part of RNs’ communication practices. Limited health literacy is associated with poor health outcomes and problematic use of healthcare services. Patients with higher levels of health literacy report better health behaviors [18], and efforts to improve health communication among healthcare providers are hence needed [19].

Moreover, communication enhancing patients’ involvement in decision-making can empower them to become active and capable in managing their own health [14, 20, 21]. Ideally, communication should be tailored to patients’ needs and expectations [22, 23]. If not, this may result in dissatisfied patients and more hospital or emergency care visits [23, 24]. A recent review study points out that there are relatively few studies on RNs’ communication practices compared to the number of studies and reviews on physician–patient communication [25]. The nursing studies predominantly focused on nurses’ provision of self-management support and patient education [26–29]. Nevertheless, enhancing RN-patient communication and decision-making in primary care can have far-reaching merits, and providing a solid research base for best practices is hence needed. This paper reports on a study protocol for such research.

### AIM

The overall objective of this research is to investigate current practices of communication and decision-making during RNs’ initial assessment of patients’ health problems in primary care, examine working mechanisms within good practices, and develop innovative and feasible solutions for an integrated care model with RNs in primary care.

The specific aims are as follows:

To investigate patients’ expectations and experiences with communication and decision-making during their first contact with an RN in primary care.To investigate patient-RN communication on the level of patient involvement.To investigate RNs’ actual communication, assessments and decision-making, value conflicts and the challenges and strategies they use in prioritizing.To analyze the underlying working mechanisms of good communication practices.To develop methodologies for facilitating efficient processes in assessing, managing, and prioritizing patients in primary care for RNs.

## Methods and analysis

### Design

This is a prospective multicenter study. Varying methods for data collection and analysis will be used to explore communication practices of patient-RN communication in primary care. The STROBE guidelines for the conduct and dissemination of observational cross-sectional studies will be used [30].

### Recruitment procedure

The study aims to collect a purposive sample of 150 patient-RN consultations, including 30 RNs and 150 patients, distributed among the RNs. Patients and RNs will be recruited at primary care centers in three geographic areas of southwest Sweden to include primary care centers in both urban and rural areas and both public and private (under contract) providers. To facilitate recruitment of participants, some of the researchers will act as local contact persons. Initially, RNs will be informed and recruited. Afterwards, the local contact person will be on site to recruit potential patients to minimize the impact on ordinary care work.

First, we will approach eligible RNs. Three researchers, one in each area, will inform RNs about the research and ask for participation. RNs will be recruited after informed consent. Eligible adult patients (aged 18 years or older) with an appointment to the participating RNs during preselected study days will be informed about the research and invited to participate by one of the researchers. Patients who are willing to participate will be asked to give written informed consent.

To assess patient-reported outcomes, patients will be asked to complete a questionnaire before and after the consultation and at the two-week follow-up (specific aim 1). To monitor communication during patient-RN visits, audio-recordings of communication during these consultations will be made (specific aim 2). To investigate RNs’ clinical reasoning, assessments made, and priorities or related value conflicts, reflective interviews individually and in focus groups will be conducted (specific aim 3). Data will be collected in 2023 and 2024 and analyzed and reported from 2023 to 2026. For an overview of the participants and data collection, see Fig. 1. The data gathered and results will be used to disentangle working mechanisms using the realist evaluation methodology [31]. This will aid in the development and design of methodologies for working processes that facilitate efficient and person-centered assessments and decision-making for the management and priority of patients in primary care by RNs (specific aims 4 and 5).

**Fig. 1 Fig1:**
[figure not shown]
Overview of participants and data

### Study size

In conformity with the explorative design, a sample size calculation was not performed, as we did not focus on a single outcome to base our power calculation on in this multiple outcome prospective study. Considering the lack of research in this area, the number of observations of patient-RN consultations was deemed sufficient and feasible, and 5 consultations per RN was considered sufficient to determine their communication style. The number of RNs was also chosen considering that a sample size of 30 can be enough to trust the confidence interval. A two-sided α of 0.05 and 95% power will be considered in the data analysis comparing patient and RN age, sex, and educational level.

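### A 95% power figure is attached to comparisons by patient and RN age, sex and education, although no sample size calculation was done and 150 consultations in 30 RNs do not give that power in general

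*Protocol article*

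**What the plan says.** The Study size section of the protocol article explains that, the design being explorative with several outcomes, "a sample size calculation was not performed, as we did not focus on a single outcome to base our power calculation on". The number of consultations is justified as sufficient and feasible. The paragraph then closes with "A two-sided α of 0.05 and 95% power will be considered in the data analysis comparing patient and RN age, sex, and educational level".

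The sample is fixed in the Recruitment procedure section: "a purposive sample of 150 patient-RN consultations, including 30 RNs and 150 patients, distributed among the RNs". That is five consultations per RN on average.

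The Audio recordings part of the analysis section recognises that consultations are nested within RNs. It plans to calculate ICCs and then consider multilevel analysis. No ICC value is given anywhere.

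The Outcome measures section says patients' sex, age and education will receive particular attention, so at least the patient-side comparisons can be expected in the reports.

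**The concern.** The opening and closing statements of the paragraph do not fit together. Power follows from the sample size, the effect to be detected, the variance and the group split. An analyst can choose alpha, but cannot choose power once the number of patients and RNs is settled. A power figure with no effect attached has no defined meaning, and the paragraph itself says no calculation produced it.

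What is at stake is how null results are read. If a comparison by age, sex or education is not significant, a reader who has seen 95% power in the published protocol may take it as good evidence of no difference. Whether that is justified depends on the size of difference the sample can detect, which the article does not state.

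**Working it through.** **Inputs from the article.** Two-sided alpha 0.05; power 95%; 150 consultations with 150 patients; 30 RNs; 5 consultations per RN.

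**Inputs not in the article, assumed here.** Results are in SD units because no outcome or SD is named. Patient splits: 75/75 and 112/38, plus 50/50 to represent 100 patients remaining. RN splits: 15/15, 24/6 and 27/3. ICC: 0.01 to 0.3. The sentence is read as comparing outcomes by these characteristics.

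**The plan's own figure.** The 95% cannot be reproduced, because no effect, SD, split or ICC is given. The formula is therefore inverted to find the difference that has 95% power.

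**Patient factors.** Normal approximation: d = (z₀.₉₇₅ + z₀.₉₅) × √(1/n₁ + 1/n₂), with z₀.₉₇₅ + z₀.₉₅ = 1.960 + 1.645 = 3.605. At 75/75: 3.605 × √(2/75) = 0.589 SD. The noncentral t gives slightly more:

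| Patients per group | Detectable at 95% power (t) |
|---|---|
| 75/75 | 0.59 SD |
| 112/38 | 0.68 SD |
| 50/50 (100 patients) | 0.73 SD |

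At 75/75, power is 86% for 0.5 SD and 45% for 0.3 SD. About 105 per group would be needed for 95% power at 0.5 SD.

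These figures treat patients as independent. If the patient factor varies within RNs and the analysis compares within RNs, the normal-approximation figure shrinks by √(1 − ICC): 0.589 × √0.95 = 0.57 SD at ICC 0.05, and 0.589 × √0.80 = 0.53 SD at ICC 0.20. So 0.59 is not the most favourable case.

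**RN factors.** All five consultations of an RN fall in the same group, so the design effect is 1 + (5 − 1) × ICC. The effective number per group is 5 × (RNs in the group) ÷ design effect. At ICC 0.1 and 15/15: 75 ÷ 1.4 = 53.6 per group, and 3.605 × √(2/53.6) = 0.70 SD. With a t distribution on 28 degrees of freedom this becomes 0.72 SD. The full set, using t with 28 df:

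| ICC | Design effect | 15/15 | 24/6 | 27/3 | Power for 0.5 SD at 15/15 |
|---|---|---|---|---|---|
| 0.01 | 1.04 | 0.62 SD | 0.78 SD | 1.04 SD | 83% |
| 0.05 | 1.2 | 0.67 SD | 0.84 SD | 1.11 SD | 77% |
| 0.1 | 1.4 | 0.72 SD | 0.90 SD | 1.20 SD | 70% |
| 0.2 | 1.8 | 0.82 SD | 1.02 SD | 1.36 SD | 60% |
| 0.3 | 2.2 | 0.90 SD | 1.13 SD | 1.51 SD | 51% |

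At 15/15 RNs, a true 0.5 SD difference would therefore be missed about 23% of the time at ICC 0.05 (100 − 77) and about 49% at ICC 0.3 (100 − 51).

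**The case against.** The strongest defence is that the study is observational and openly explorative, that no confirmatory test depends on this sentence, and that it says power will be considered, not that it is achieved. The clustering is also acknowledged, with ICCs to be calculated. All of this stands, and it lowers the weight of the point. It does not rescue the figure: an explorative study that did no calculation has no need of a power statement, and this one gives the reader nothing to attach the 95% to.

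Three stronger readings are tempting, and the article does not support them.

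- A reader might infer that the study can detect only large differences. That does not fit patient factors, where the threshold is about 0.53 to 0.59 SD at an even split and power for 0.5 SD is already 86%. For RN factors it becomes a fair description only at an ICC of about 0.2 or more, or with uneven splits.
- A reader might take "a sample size of 30 can be enough to trust the confidence interval" as a mistaken claim of precision. Trusting an interval most naturally means trusting its coverage. It is a hedged rule of thumb and says nothing about width.
- A reader might see a conflict between "5 consultations per RN was considered sufficient to determine their communication style" and the precision of RN-level comparisons. That conflict appears only if one imposes a reliability threshold, and the article sets none. Nor does the article propose to classify or rank individual RNs.

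**Conclusion.** The point holds for the 95% power statement alone. The article attaches the figure to comparisons by patient and RN age, sex and education while saying that no calculation was made, and the fixed sample does not have that power as a general property.

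The size of the gap depends on the factor. For patient factors it is modest: about 0.6 SD is needed at an even split without attrition, rising to 0.68 SD at 112/38 and 0.73 SD with 100 patients. For RN factors it is wider: about 0.6 to 0.9 SD at 15/15, and more than 1 SD at 27/3. These figures rest on assumed splits, ICCs and attrition, since the article gives none. That the number has no stated basis does not depend on those assumptions.

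Severity is moderate. The sentence affects how null findings would be read; it does not undermine the design or a primary analysis.

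**What to change.** In the Study size section, delete the 95% power and keep the two-sided alpha of 0.05. Replacement wording could be: *The sample was set by feasibility. Comparisons by patient and RN age, sex and educational level are exploratory and will be reported as estimates with 95% confidence intervals that account for clustering by RN. A non-significant result will not be taken as evidence of no difference.*

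If the authors wish to quote detectable differences, each should carry its assumed group split, ICC and attrition. A single range without them would be too favourable for an unevenly distributed RN characteristic or for the two-week follow-up data. The sentences on 30 RNs and on five consultations per RN can stay.

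The cost is wording only: no more patients, RNs or data collection. The stated figure becomes less favourable.

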### Outcome measures

The outcomes are communication practices of first patient-RN encounters in primary care in relation to:

Patient-reported expectations and experiences (Questionaries).Communication processes and patient involvement (Audio recordings).Assessment and decision-making processes and related priorities and value conflicts (Interviews).

For an overview of outcomes related to the respective data to be collected, see Fig. 2.

**Fig. 2 Fig2:**
[figure not shown]
Overview of outcomes related to data sources

As the need for and experiences of communication and decision-making are likely to be influenced by patient-related factors, specific attention will be given to the mediating role of patients’ sex, age and level of education and the nature of their health problems.

### Data collection

#### Patient questionnaires

The patient-reported data on expectations and experiences will be gathered at three different time points designed to meet the patients’ experiences prior to the consultation, immediately after, and two weeks after an RN visit. The previsit questionnaire assesses demographics (year of birth, sex, native language and current health problem and the reason for encounter), patients’ expectations of the visit using the QUOTE-COMM (expectations) (QUality Of care Through the patients’ Eyes) [32, 33], and their functional health status using the COOP/WONCA [34, 35]. The postvisit questionnaire includes the QUOTE-COMM (experiences), satisfaction with the consultation and experienced quality of care. The telephone follow-up questionnaire includes the QUOTE-COMM, functional health status using the COOP/WONCA, satisfaction and quality of care.

*The QUOTE-COMM* measures patients’ expectations and experiences with different communication aspects and has been found to be feasible and useful [33]. A total of 19 items, related to three scales, are scored on a 4-point Likert scale. The three scales are a task-oriented scale (6 items) on different medical content, an affect-oriented scale (7 items) on emotional aspects of the interaction, and a therapy-oriented scale (6 items) on therapeutic aspects. Before the consultation, patients score the importance of different communication aspects, e.g., their expectations. After the consultation, patients score the RNs’ performance related to the communication aspects, e.g., their experiences. At telephone follow-up, patients will score their satisfaction with the communication aspects.

*The COOP/WONCA* measures a person’s functional health status on six charts related to six aspects of functioning: physical fitness, feelings, daily activities, social activities, change in health, and overall health. These aspects are rated on a five-point ordinal scale ranging from 1 (better/no limitation at all) to 5 (worse/severely limited), with reference to the last two weeks. Each aspect is reported on a single chart that has a title, a question and a response scale illustrated with easily understandable drawings.

For the assessment of experiences of overall satisfaction and quality of care, a numeric rating scale is used ranging from 1 (very dissatisfied/low quality of care) to 10 (extremely satisfied, very high quality of care). Patients will respond to two questions on (1) their overall experience of satisfaction with the consultation and (2) their experience of quality of care of their consultation.

#### Audio-recordings (ARs)

Observations of real-time consultations will be made with data collected on AR to explore practices of patient-RN communication on health concerns and needs and patient involvement. ARs are coded with OPTION^5^, observing patient involvement in decision-making [36, 37] and the Verona Coding definition of emotional sequences (VR-CoDES) [38, 39]. The ARs will be made by the RNs after receiving information about how to manage these recordings. No researchers will be present during consultations to minimize the impact of the research on the visit. ARs provide powerful, real-life data that allow for analysis of communication and interaction between patients and RNs in their natural context. Analysis of such empirical data on real-time consultations can provide new insights into RNs’ communication practices, in contrast to interviews where there might be gaps between what people report and what they can recall from a situation [40].

#### Interviews

Individual interviews and focus groups with RNs will be used for data collection. All interviews will be audio-recorded and transcribed verbatim. The interviews will be performed during RNs working hours at the primary care centers.

To explore RNs’ clinical reasoning in prioritizing the needs of the individual patient, data will be collected with individual qualitative interviews using stimulated recalls. A purposive sample of the nurses, e.g., 15, will be selected for the interviews with various characteristics of the RNs, their patients, and the consultation. These interviews will be conducted 2–4 weeks after consultation. Each RN will be asked to respond to and elaborate on their conversation with the patient and their clinical reasoning and assessment made during one of their previous consultations during these interviews. Sequences from the ARs will be used to stimulate recall and reflections on their thoughts and actions during the consultation. The RNs will be encouraged to make free and indirect comments about their consultations, while open-ended follow-up questions will be used to obtain as detailed and nuanced descriptions as possible about their clinical reasoning. When needed, the ARs can be stopped. Stimulated recall is a useful method to study consultations [41]. This enables us to further investigate RNs’ communication strategies, their interaction with patients and their clinical reasoning.

To get RNs to reflect and discuss their experiences of clinical reasoning and priorities in patient-RN consultations, data will be collected using four to six focus groups with a total of 30 RNs. A convenience sample of RNs will be selected. This includes both RNs who have previously participated in the research and RNs who have not. Before the interviews, participants will have access to a short text summarizing the findings on RNs assessment from individual interviews. Using focus groups in this way will allow for co-creation and further development of the first analysis from data collected by individual interviews. Four to six RNs will be included in each focus group. The RNs will be asked about challenges and potential conflicts of goals when making assessments and priorities or consequences related to these. Focus groups allow participants to discuss and compare their experiences, which makes it possible to obtain rich descriptions of the phenomenon in focus [42], e.g., their experiences of aspects important for their clinical reasoning and assessments made and challenges and prerequisites for priorities or related value conflicts. A semi-structured interview guide and follow-up questions will be used.

